# Understanding the impact of five major determinants of health (genetics, biology, behavior, psychology, society/environment) on type 2 diabetes in U.S. Hispanic/Latino families: Mil Familias - a cohort study

**DOI:** 10.1186/s12902-019-0483-z

**Published:** 2020-01-06

**Keywords:** Type 2 diabetes, Hispanic Americans, Latino, Social determinants of health

## Abstract

**Background:**

In the United States (U.S.), the prevalence of both diagnosed and undiagnosed type 2 diabetes (T2D) is nearly twice as high among Mexican-origin Hispanic/Latino adults compared to non-Hispanic Whites. Rates of diabetes-related complications, e.g., acute stroke and end-stage renal disease, are also higher among Hispanic/Latino adults compared to their non-Hispanic/Latino White counterparts. Beyond genetic and biological factors, it is now recognized that sociocultural influences are also important factors in determining risk for T2D and the associated complications. These influences include ethnicity, acculturation, residence, education, and economic status. The primary objective of this study is to determine the influence of the 5 major determinants of human health (genetics, biology, behavior, psychology, society/environment) on the burden of T2D for Latino families*.* To achieve this objective, Mil Familias (www.milfamilias.sansum.org/) is establishing an observational cohort of 1000 Latino families, with at least one family member living with T2D.

**Methods:**

Specially trained, bilingual Latino/a community health workers (Especialistas) recruit participant families and conduct research activities. Each individual family member will contribute data annually on over 100 different variables relating to their genetics, biology, psychology, behavior, and society/environment, creating a Latino-focused biobank (“Living Information Bank”). This observational cohort study is cross-sectional and longitudinal. Participants are divided into 4 groups: adults age ≥ 18 years with and without T2D, and children age ≥ 7 and < 18 years with and without T2D. Study activities take place through encounters between families and their Especialista. Encounters include screening/enrollment, informed consent, health promotion assessment, laboratory tests, questionnaires, physical activity monitoring, and reflection.

**Discussion:**

By creating and providing the framework for the Cohort Establishment study, we intend to inform new approaches regarding equity and excellence in diabetes research and care. We will examine the complex set of factors that contribute to the burden of diabetes in Latino families and assess if cardio-metabolic disease risks go beyond the traditional biological and genetic factors. Breaking the code on the interplay of cardio-metabolic risk factors may help not only this fast growing segment of the U.S. population, but also other high-risk populations.

**Trial registration:**

Study retrospectively registered at ClinicalTrials.gov (NCT03830840), 2/5/2019 (enrollment began 2/1/2019).

## Background

In the United States (U.S.), members of racial and ethnic minority groups are disproportionally affected by type 2 diabetes (T2D). For example, the prevalence of both diagnosed and undiagnosed T2D is nearly twice as high among Mexican-origin Hispanic/Latino adults compared to non-Hispanic Whites [1]. Furthermore, the American Heart Association has reported that only 14% of adult Hispanic/Latino Americans meet the criteria for “ideal cardiovascular health” as compared to 20% for non-Hispanic/Latino White Americans [2]. Rates of diabetes-related complications including premature death from diabetes, acute stroke and end-stage renal disease are also higher among Hispanic/Latino adults compared to their non-Hispanic/Latino White counterparts [3].

Beyond genetics and biological factors, such as achieved hemoglobin A1_c_ (HbA_1c_) levels, lipids, obesity and blood pressure, it is now recognized increasingly that sociocultural influences are also important factors in determining an individual’s risk related to the development of T2D and the associated complications. These influences include ethnicity (e.g., Mexican-Americans have a greater diabetes burden than Cuban-Americans); duration and impact of acculturation (the process by which immigrants adopt the attitudes, values, customs, beliefs, and behaviors of a new culture); place of residence; achieved education level; and economic status [4, 5]. Compounding this burden, Hispanic/Latinos are also a minority among diabetes care providers, researchers, or research participants. For example, Hispanic/Latinos represent just 1% of clinical trial participants, and Hispanic/Latinos are a small fraction of providers (e.g., Hispanic/Latinos are about 40% of California’s population but only 8% of nurses and 5% of doctors) [6, 7]. Therefore, given the previous lack of Hispanic/Latino participation in clinical research, this study aims to (a) find novel approaches to engage this population and (b) consider psychological, behavioral and environmental factors, as well as the traditional biological and genetic influences on the risk of progression of T2D in this growing but underserved U.S. population, as these have not be undertaken previously.

## Methods/design

In this study, we acknowledge the use of the term “Hispanic/Latino” when referring to individuals because they identify as persons of Latin American descent who live in the U.S. or Latin America and trace their origin to countries in the Americas where the predominant languages are Spanish, Portuguese, and French [4]. But henceforth we refer to study participants as “Latino(s)” to be inclusive of participants of Latin American origin who do not speak Spanish.

### Aims

*The primary objective of this study is to determine the influence of the 5 major determinants of human health (genetics, biology, behavior, psychology, society/environment) on the real-world burden of T2D for Latino families.* To achieve this objective, beginning February 2019, Mil Familias (www.milfamilias.sansum.org/) began the establishment of an observational cohort of 1000 Latino families with at least one family member currently living with T2D, among whom we are studying the impact over time of the 5 main determinants of human health. We work with specially trained, bilingual Latino/a community health workers (known as Especialistas) who recruit participant families, conduct research activities including data collection, and, when necessary, refer families to appropriate community resources. Facilitated by these Especialistas, each individual family member contributes data annually on over 100 different variables relating to their genetics, biology, psychology, behavior, and society/environment, creating a Latino-focused biobank (“Living Information Bank”). Once the cohort is established, data analyses will inform the development of evidence-based, collaborative, and culturally-relevant prevention and treatment strategies.

An operational pilot involving over 100 adult Latino individuals with T2D, completed in 2018, established the feasibility of methods and created the infrastructure to scale to the 1000-family cohort (Mil Familias-Santa Barbara’s Operational Pilot to Understand Diabetes in the Latino Community NCT03736486).

### Primary outcome

The primary outcome of Mil Familias cohort establishment is the creation of an observational cohort of 1000 Latino families with at least one family member living with T2D, by deploying the methods proven feasible by Mil Familias Operational Pilot. The Mil Familias Cohort Establishment will expand upon the Mil Familias Operational Pilot cohort and infrastructure to collect and store the up to 100 proposed variables across the 5 determinants of human health (genetics, biology, behavior, psychology and the environment) to support long-term Mil Familias implementation. The variables pertaining to each participant are collected and stored during an initial visit series and then annually for up to 3 years.

### Major secondary outcomes

These include (a) achieved HbA_1c_ levels; (b) cardio-metabolic risk including blood pressure, waist circumference, and insulin sensitivity; (c) food security; and (d) activity levels. Details of additional secondary end-points have been published previously (https://clinicaltrials.gov/ct2/show/NCT03830840).

In addition to the variables listed above, we also collect prospective data related to major cardiovascular events (3-point MACE: cardiovascular death, non-fatal myocardial infarction and non-fatal stroke). Data sources include participants and their families, collaborating health centers, and the local provider of in-hospital clinical care. At enrollment, participants provide written, informed consent for Mil Familias researchers to request data from the relevant provider organization’s electronic medical record system on reported clinical events. Additional information are collected on new onset diabetes including gestational diabetes, unscheduled attendances at emergency rooms, and hospital admissions due to uncontrolled diabetes.

### Design

The study is an observational cohort trial that is cross-sectional and longitudinal. Participants are divided into groups by age and diabetes status (described below). The overall design is shown in Fig. 1.

**Fig. 1 Fig1:**
[figure not shown]
Study design. Encounters may be split or combined as long as the Reflection encounter occurs at least 3 months after the HPA encounter

### Setting and participants

In Santa Barbara County, the population is 45.6% Latino, most of Mexican ancestry [8]. To establish the Mil Familias cohort, up to 1200 families may be screened and enrolled with an estimated 20% screen-fail or dropout rate, resulting in approximately 1000 families in the study. Potential participants are selected from Santa Barbara County and surrounding communities or satellite sites with the help of existing community allies and healthcare organizations. Approaches to recruitment include engagement with and referrals from: local Federally Qualified Health Centers (FQHCs); community service providers; academic institutions with high English as a Second Language enrollment (i.e., Hispanic Serving Institutions); local employers; local media (Spanish and English language); social media; advertisements; participation in community events; SDRI physical site and websites; and ad hoc interaction with Especialistas. This type of combined approach was successful in the operational pilot. Only participants who meet all eligibility criteria are enrolled and study staff confirm participant eligibility during the screening and enrollment encounter. A “family” is followed as one unit, but is estimated to include on average 3 to 5 individuals (based on findings from the operational pilot). Therefore, up to 6000 individuals may be screened and enrolled.

The definition of “Mil Familias family” accounts for statistical, tracking, and reporting requirements of this study and is based on the U.S. Census definition of a “family group” and modified to include single-person units and relatedness via domestic partnership [9]. Each individual may participate in just one Mil Familias family. A “Mil Familias family” consists of an enrolled individual family representative and any enrolled family members. The family representative is the first enrolled. A family member is any individual subsequently enrolled who: (a) resides with the family representative (i.e., co-resides) and (b) is an immediate relative (spouse/partner, parent, child, or sibling) to the family representative by birth, marriage/domestic partnership, or adoption.

**Inclusion Criteria** (family representative)
Males or females ≥ 7 years of age at enrollment.Self-reported Hispanic/Latino heritage.Co-resides with immediate family member (as defined above) or self with established diagnosis of T2D.Signed and dated written informed consent by the date of enrollment.Based on the research staff’s judgment, participant or participant’s representative must have a good understanding, ability, and willingness to adhere to the protocol, including performance of self-monitored data collection during the wearable device portion of the study.

**Inclusion Criteria** (family member)
Males or females ≥ 7 years of age at enrollment.Self-reported Hispanic/Latino heritage.Co-resides with immediate family representative.Signed and dated written informed consent by the date of enrollment.Based on the research staff’s judgment, participant or participant’s representative must have a good understanding, ability, and willingness to adhere to the protocol, including performance of self-monitored data collection during the wearable device portion of the study.

**Exclusion Criteria**
Life expectancy < 6 months.Any active clinically significant physical or mental disease or disorder, which in the investigator’s opinion could interfere with the participation in the study.Language barriers precluding comprehension of study activities and informed consent.Participation in other research studies involving medication or device within 1 month prior to enrollment.Known or suspected abuse of alcohol, narcotics, or illicit drugs.

**Participant Groups**

Individual participants are assigned to a data collection group stratified by age and T2D status, as follows. The group serves to identify the type of data collected for that individual.
Group 1 consists of adults aged ≥ 18 years with T2D.Group 2 consists of adults aged ≥ 18 years without T2D.Group 3 consists of children aged ≥ 7 years and < 18 years with T2D.Group 4 consists of children aged ≥ 7 years and < 18 years with T2D without T2D

### Especialistas

The Mil Familias Operational Pilot proved the feasibility of Sansum Diabetes Research Institute’s (SDRI’s) “Especialista” model, in which bilingual Latino/a community health workers are trained by SDRI in diabetes identification, research methodology, and referrals to healthcare and other social needs resources, and then employed to conduct research.

Upon enrollment, each family is paired with an Especialista who speaks their preferred language/s (Spanish and/or English). Individuals meet face-to-face with their Especialista as well as have access via email or phone to their Especialista while enrolled in the study. Especialistas facilitate research activities, which include administering the informed consent and conducting study encounters. The encounters involve delivering questionnaires, conducting interviews, and training on wearable devices. Especialistas may facilitate participant connections to research, education, and care opportunities relevant to preventing and managing diabetes, and address barriers to accessing such resources by serving as a trusted community member contact and liaison with research staff. The research team meets with the Especialistas on a weekly basis for debriefing on study progress as well as for continuing education.

### Enrollment

Enrollment begins with the informed consent process. Participant eligibility is confirmed following review of the inclusion and exclusion criteria by study staff during the Enrollment Encounter. Each participant is provided with oral and written information (English and/or Spanish) describing the nature and duration of the study. Prior to initiation of any study-related procedures, the participant signs and dates a written informed consent to participate in the study, including the California Experimental Subject’s Bill of Rights and Health Insurance Portability and Accountability authorization forms. These forms are retained with SDRI records, and each participant receives a copy. For minor participants (aged ≥7 years and < 18 years), both participant and parent receive study information; the participant’s parent signs on behalf of the minor participant and the minor signs an assent form.

The participant is assigned and given contact information for their Especialista who is their point of contact for Mil Familias. An emergency telephone number is also provided, as well as the SDRI contact information for non-urgent assistance during normal business hours. Participants are instructed to contact the research staff if they experience any adverse events or untoward occurrences while enrolled in the study. Participants are provided with a unique study identifier. They are asked to bring this identifier with them to all Mil Familias encounters.

After the informed consent process, data collection begins, including administration of a brief introductory interview and collection of basic sociodemographic information. The Especialistas schedule the participant’s next visit.

### Study activity series and scheduling encounters

Study activities take place through face-to-face interaction between families and study staff; these visits are referred to as “encounters.” Encounters are organized into “series,” with activities varying based on whether the series is for a new participant or a continuing participant. Each new participant completes an initial encounter series, including screening/enrollment and informed consent, Health Promotion Assessment (HPA), laboratory tests, questionnaires, and reflection, as well as physical activity monitoring and interaction with the Especialista with whom they are paired. After having been enrolled in the study for at least 12 months, participants are eligible to start the continuing participant encounter series. The continuing participant encounter series involves activities similar to the new participant encounter series. While continuing participation is preferred, it is not required to be eligible for the study.

In the course of this 3-year protocol, participants will complete at least 1 new participant encounter series and, possibly, 0, 1, or 2 continuing participant encounter series, depending on their initial enrollment date. Regardless of series type (new participant or continuing participant), participants have the flexibility to complete encounters in accordance with their personal schedules as long as encounter series are completed in chronological order. The last encounter, Reflection, in a 12-month participation cycle occurs at least 3 months after the HPA encounter.

Families may attend study encounters as a group, but individual data collection and informed consent occurs one-on-one in a private setting, unless the participant is a minor. As detailed above, participants are assigned to a data collection group based on their age and diabetes status.

### Health promotion assessment (HPA) and biological specimen collection encounter

Height, weight, and waist circumference are measured following the guidelines in the National Health and Nutrition Examination Survey Anthropometry Procedure Manual, January 2016 [10]. Body mass index is then be calculated. Blood pressure is measured following 2017 guidelines set forth by the American College of Cardiology/American Heart Association Task force on Clinical Practice Guidelines [11]. A foot screening is performed by trained Especialistas with medical provider guidance.

In addition, participants meet with qualified, trained study staff and, depending on age, diabetes status, and personal preferences, the following biological specimens may be collected:
Epithelial cell sample via cheek swab to collect genetic material [DNA Genotek, Ontario, Canada, or Salimetrics, Carlsbad, CA, USA]Saliva sample to collect genetic material [DNA Genotek, Ontario, Canada or Salimetrics, Carlsbad, CA, USA]Urine sample to assess protein levels and potential kidney damage (laboratory screening sample)*Stool sample to analyze bacteria lining the digestive tract for microbiome genomic testing [DNA Genotek, Ontario, Canada or Fecal Occult Blood Test, Beckman Coulter, Brea, CA, USA]Finger-stick HbA_1c_ test [Siemens DCA Vantage, Siemens Healthcare, Norwood, MA, USA]

*Note: Urine samples may be collected at the HPA or Laboratory Encounter.

### Laboratory encounter

Participants meet with trained study staff, (e.g. licensed phlebotomist) for laboratory tests that may include:
Urine sample to assess protein levels and potential kidney damage (laboratory screening sample)*Fasting venous blood draw, which is analyzed immediately for complete blood count (no differential) panel, HbA1c, comprehensive metabolic panel, lipid panel, thyroid panel, C-peptide, C-reactive protein quantitative, and insulin, and other samples are transported to the Mil Familias biobank for processing, storage, and future analysis.

The blood drawing limit is determined for all participants based on the participant’s age, weight, and blood draw history; volume per draw is determined based on NIH Guidelines for Clinical Research Purposes [12], and in consultation with the Principal Investigator if needed.

Blood collection is done in a fasting state (at least 8 h), unless the participant takes insulin. Only certified personnel perform blood collection. Blood is drawn into evacuated blood collection tubes for the requested laboratory tests and for biobank storage. One 10 ml red top and one 10 ml lavender top with EDTA is drawn with the tubes inverted 6–8 times. The EDTA lavender top tube is then centrifuged (2000 g for 20 min) as soon as possible after collection. Serum red top tubes sit at room temperature for at least 30 min and not longer than 2 h before centrifugation. Biobank samples are processed within 4 h of the draw. Plasma, serum, and buffy coat or leukocytes are separated into sterile storage cryotubes, identification labels are attached, and samples are placed in a − 80 °C freezer with constant remote temperature monitoring.

### Questionnaires

Questionnaires are completed by select Mil Familias participants depending on age, diabetes status, and whether the participant is a new or continuing participant. This encounter may take place either at SDRI, a partner medical clinic, or at a community location. The Especialista verbally administers and, if necessary, assists with the participant-reported questionnaires. Questionnaires for participants include topics that cover the 5 major determinants of health: genetics, biology, behavior, psychology, and society/environment (Additional file 1).

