### Activity monitoring

Participants aged 13 years and over are asked to wear wearable activity monitor/s each day for up to a week and up to twice within a 12-month period, with at least 6 months between each wear period. The purpose of this stratification is to capture activity during the spring-summer season versus the fall-winter season.

The Especialista and/or research staff dispense the wearable device/s to the participant and train them on how to use the wearables. Participants wear a Fitbit Charge 2™ (Fitbit, Inc., San Francisco, CA) (or a similar Fitbit activity tracker) on the non-dominant wrist and an ActiGraph wGT3X-BT (ActiGraph, LLC, Pensacola, FL) monitor on the dominant hip. Participants are asked to wear the Fitbit at night, and the ActiGraph can be removed at night and replaced in the morning. After dispensing the device/s, each participant or their representative fills in an activity questionnaire to distinguish physical activity relating to the participant’s occupation from physical activity via leisure-time exercise. Participants are asked to return the wearable device/s after one week. Both devices are then downloaded to a computer at the study center; Fitbits are not wirelessly synchronized to a mobile phone application. Adherence is defined as ≥12 h/day of wear time for at least 3 of the 7 days, and the 3 days of wear was chosen to represent approximately half of the possible wear time. Upon return of wearable device/s, each participant or their representative may complete an Activity Monitor Follow-up Survey.

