#### Data analysis

Statistical analyses will be performed in collaboration with SDRI’s data partner, Santa Barbara Actuaries, Inc. All statistics will be considered significant with *p* values < 0.05. Chi squared tests will be conducted to detect differences in categorical outcomes. T-tests will be conducted to test differences in continuous outcomes where the sample size is less than 50 for any sub population. Z tests will be conducted for continuous variables with a sample size greater than 50 where there is no evidence of violation of normality. For continuous outcomes that may violate the normality assumption, a log-normal transformation or other appropriate analysis may be applied.

In addition, independent variables may be confounders of each other’s effect on the outcomes and thus consideration will be given to explore likely confounders. There are adjustment approaches, such as propensity score matched cohorts, to address such biases. Regression analysis for a particular outcome can also be performed on various individual characteristics.

Based on the experience from the Operational Pilot, we expect the sample size of the full study to be sufficient to provide substantial levels of statistical significance to compare the relationship between outcomes and individual variables. For example, based on the Operational Pilot (*n* = 107), HbA_1c_ can be stratified into 2 groups (> 9 and < 7%). In the Pilot, we found that 40% had an HbA_1c_ < 7%, and for 28% it was > 9%. This was significant at the 3% level and this will fall below 1% with 160 participants and below 0.1% at 280. Our full study population is designed to have 1000 members, so we believe that the majority of individual variables of interest will be powered to show statistically significant conclusions.

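### Questionnaires are read out by the Especialista paired with each family, but the named chi-squared, t and Z tests have no Especialista term, so interviewer differences can appear as effects of questionnaire-based variables

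*Protocol article*

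**What the plan says.** All references are to the protocol article.

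- **Pairing.** The Especialistas section says that "each family is paired with an Especialista who speaks their preferred language/s". The unit of assignment is the family, so Especialista sits above family in the data structure.
- **Role.** The Aims section describes Especialistas as workers "who recruit participant families, conduct research activities including data collection".
- **Mode.** The Questionnaires section says "The Especialista verbally administers and, if necessary, assists with the participant-reported questionnaires". It also limits who is asked: "Questionnaires are completed by select Mil Familias participants depending on age, diabetes status, and whether the participant is a new or continuing participant".
- **An exception.** Under Activity monitoring, "each participant or their representative fills in an activity questionnaire", so not every form is read aloud.
- **Instruments.** Tables 1 and 2 list PHQ-9, ACES, PEDQ-CV, DAST-10, the Trust in Physician Scale and the Food Security Survey Module for both adult groups and for neither child group. Food security is also one of the major secondary outcomes.
- **Analysis.** The Data analysis section says "Chi squared tests will be conducted to detect differences in categorical outcomes", and that t or Z tests will be used for continuous outcomes, all at the 5% level. It adds that confounding among the independent variables will be considered, with propensity matching as one approach, and that regression on individual characteristics can be done. Neither Especialista nor clustering is mentioned.

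**The concern.** Answers on depression, drug use, childhood adversity, discrimination or trust can depend on who asks. If one Especialista draws out franker answers than another, that difference is shared by all members of all families in the caseload. The named tests treat those answers as independent.

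Two things can follow. First, precision: for any determinant whose distribution differs between caseloads, the standard error is too small and the 5% level is exceeded. Second, bias: when determinant and outcome are both told to the same interviewer (discrimination and food security, for example), a shared reporting style can create an association by itself. Accounting for households alone would remove neither, because the shared component lies above the household.

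The primary objective is to relate determinants to disease burden, and many of the psychological, behavioural and social determinants are questionnaire scores. Those are the associations at stake.

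**Working it through.** The article states no design effect, interviewer variance or number of Especialistas, so there is no figure of its own to reproduce on this point. The calculation below shows a range under stated assumptions.

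**Inputs**
- From the article: one Especialista per family; verbal administration; two-group tests at 5% (taken as two-sided, since the article does not say); 1000 families.
- Assumed: 3000 adult respondents and 10 to 20 Especialistas, so m = 3000/20 = 150 to 3000/10 = 300 adults each.
- Assumed: ICC of questionnaire answers within an Especialista, ρ = 0.01 to 0.03.
- Assumed: ICC of the determinant within an Especialista's caseload, ρx = 1 (constant within a caseload) or 0.1 (varies mostly within it).

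**Formulas**
- Design effect: DEFF = 1 + (m − 1) × ρ × ρx
- Understatement of the standard error: √DEFF
- True size of a nominal 5% test: 2 × P(Z > 1.96/√DEFF)

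**Determinant constant within a caseload (ρx = 1)**
- m = 150, ρ = 0.01: DEFF = 1 + 149 × 0.01 = 2.49; √2.49 = 1.58; 1.96/1.58 = 1.24; true size 21.4%.
- m = 300, ρ = 0.03: DEFF = 1 + 299 × 0.03 = 9.97; √9.97 = 3.16; 1.96/3.16 = 0.62; true size 53.5%.

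**Determinant varying mostly within a caseload (ρx = 0.1)**
- m = 150, ρ = 0.01: DEFF = 1 + 149 × 0.01 × 0.1 = 1.149; √1.149 = 1.072; 1.96/1.072 = 1.83; true size 6.7%.
- m = 300, ρ = 0.03: DEFF = 1 + 299 × 0.03 × 0.1 = 1.897; √1.897 = 1.377; 1.96/1.377 = 1.42; true size 15.5%.

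**Sensitivity to the assumed size.** The Data analysis section speaks of a study population of 1000 members. With 1000 respondents, 10 to 40 Especialistas (m = 100 to 25) and ρ = 0.005 to 0.05:
- ρx = 1: DEFF from 1 + 24 × 0.005 = 1.12 to 1 + 99 × 0.05 = 5.95; true size 6.4% to 42%.
- ρx = 0.1: DEFF from 1.01 to 1.50; true size 5.1% to 10.9%.

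These figures cover precision only. They do not include the bias that arises when determinant and outcome share an interviewer's style. A determinant fully balanced across caseloads (ρx near 0) is hardly affected.

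**The case against.** The strongest objection is that this is a condensed article and an interviewer term is the sort of detail left to an analysis plan. That would settle the matter if the Data analysis section were silent. It is not: it commits to specific tests that assume independence, and its open wording on confounders and regression concerns the independent variables and individual characteristics. Especialista is neither, and does not appear in Tables 1 and 2. The objection does limit the claim to what the named tests do; it cannot be said that no analysis will ever account for the Especialista.

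The second objection is that the protocol already controls interviewing: standard procedures, structured Especialista training and a triple check of the data (Quality control of data collection), weekly debriefing (Especialistas), and private one-to-one data collection for adults (Study activity series and scheduling encounters). These may well reduce interviewer variation, which argues for the lower end of the assumed ICC range. They cannot show that it is zero, and a check from collection to entry does not detect how a question was asked.

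Several stronger readings are tempting and are not supported:
- A reader might infer that every questionnaire is read aloud. Only selected participants complete questionnaires, and the activity questionnaire is filled in by the participant or a representative.
- A reader might infer that each Especialista recruits and then interviews a single neighbourhood or network. Setting and participants lists many recruitment routes, with contact through Especialistas as only one. Pairing is described by language, and nothing says that the recruiter becomes the paired Especialista.
- A reader might infer that interviewer differences will be reported as differences between families. No between-family contrast is specified; the stated target is the relation between outcomes and individual variables. No interviewer effect is documented either.
- A reader might extend the point to HbA1c, because the Discussion credits community health workers with better diabetes control. That passage describes other programmes; it does not show that outcomes here differ by Especialista.

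**Conclusion.** The point holds in a limited form. Pairing by family, verbal administration and tests without an Especialista term are all in the text, and together they leave questionnaire-based associations open to interviewer effects and understated standard errors. The exposed variables are food security among the major secondary outcomes, and scales such as PHQ-9, DAST-10, ACES, PEDQ-CV and Trust in Physician. Cohort creation, laboratory values and device-measured activity are not exposed to interviewing style.

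The size cannot be derived from the article. Under the assumptions above, inflation is moderate for most determinants, which are personal or household variables that can vary within a caseload: a true size of about 7% to 15% in place of 5%. The 21% to 53% range is a worst case for determinants constant within a caseload and should not be read as typical. With fewer respondents per Especialista the effect shrinks, to about 5% to 11% in the smaller setting. This should be changed because the remedy is cheap and better than the stated tests; it does not invalidate the study.

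**What to change.** 1. Carry the identifier of the Especialista who conducted each encounter into the analysis file. Record it by encounter rather than by family, since staff may change over the years of follow-up and a missing identifier may be hard to reconstruct later.
2. For every association in which the outcome or the determinant is a questionnaire variable, replace the chi-squared, t or Z test with a regression that includes an Especialista effect (fixed or random) above the family level.
3. Report each such result with and without the Especialista effect. Pairing by language may tie Especialista to acculturation, in which case adjustment could remove part of a real difference. Because the Especialistas are described as bilingual, that tie may be weak; the paired results would show whether it matters.
4. State the number of Especialistas and the estimated ICCs in the report.

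The cost is analysis wording, an identifier that the pairing should already provide, and a few degrees of freedom (9 to 19 for a fixed effect with 10 to 20 Especialistas). The real downside is lower precision for determinants that differ mainly between Especialistas. The mode of administration need not change: the Discussion gives a reason for it, namely trust, and an optional second mode would bring a mode difference of its own.
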